## Abstract

**Background:**

Both acute and overuse injuries are common among recreational volleyball players, especially finger/wrist, ankle, shoulder and knee injuries. Consequently, an intervention (‘VolleyVeilig’) was developed to prevent or reduce the occurrence of finger/wrist, shoulder, knee and ankle injuries among recreational volleyball players. This article describes the design of a study evaluating the effectiveness of the developed intervention on the one-season occurrence of finger/wrist, shoulder, knee and ankle injuries among recreational adult volleyball players.

**Methods:**

A randomized prospective controlled trial with a follow-up period of one volleyball season will be conducted. Participants will be healthy recreational adult volleyball players (18 years of age or older) practicing volleyball (training and/or match) at least twice a week. The intervention (‘VolleyVeilig’) consists of a warm-up program based on more than 50 distinct exercises (with different variations and levels). The effect of the intervention programme on the occurrence of injuries will be compared to volleyball as usual. Outcome measures will be incidence of acute injury (expressed as number of injuries per 1000 h of play) and prevalence of overuse injuries (expressed as percentage).

**Discussion:**

This study will be one of the first randomized prospective controlled trials evaluating the effectiveness of an intervention on the occurrence of both acute and overuse injuries among recreational adult volleyball players. Outcome of this study could possibly lead to the nationwide implementation of the intervention in all volleyball clubs in The Netherlands, ultimately resulting in less injuries.

**Trial registration:**

Dutch Trial Registration NTR6202, registered February 1st 2017. Protocol: Version 3, February 2017.

## Background

Volleyball is one of the most popular sport in the world [1]. Besides its beneficial health effects, volleyball is also associated with a risk for musculoskeletal injuries, either acute or overuse injuries [2–4]. The incidence of musculoskeletal injuries among volleyball players ranges from 1.7 to 10.7 injuries per 1000 playing hours, occurring mostly in the fingers/wrists, shoulders, knees and ankles [2–4]. These injuries might induce impairments in daily life, sport and/or work and lead to substantial direct and indirect healthcare costs [5]. Consequently, integral measures to prevent or reduce the number of musculoskeletal injuries among volleyball players are needed.

Accordingly, a scientific research project together with the Dutch Volleyball Federation (Nevobo) has started in The Netherlands (funded by ZonMW, the Netherlands Organization for Health Research and Development). Aims of this project are (i) to develop an evidence-based intervention to prevent the occurrence of finger/wrist, shoulder, knee and ankle injuries among young and adult recreational volleyball players, and (ii) to evaluate the effectiveness of the developed intervention. After the systematic development of ‘VolleyVeilig’ as an intervention to prevent the occurrence of musculoskeletal injuries among recreational volleyball players, the next step is to assess its effectiveness within a randomised prospective controlled trial. This article describes the design of such a study.

## Methods/design

The CONSORT statement is followed to describe the design of the study [6]. This statement is a checklist intended to improve the quality of reports of randomized controlled trials.

### Objective and hypothesis

The objective of the study is to evaluate the effectiveness of the developed intervention (‘VolleyVeilig’) on the one-season occurrence of finger/wrist, shoulder, knee and ankle injuries among recreational adult volleyball players. Analogous to previous studies about the effect of preventive interventions in volleyball [7] and in other sports [8, 9], the hypothesis of this study is that the developed intervention will lead to a 40% reduction of the number of musculoskeletal injuries over the one-season follow-up in the intervention group by comparison to the control group.

### Study design and allocation

A randomized prospective controlled trial with a follow-up period of one volleyball season (September, 2017 – June, 2018) will be conducted (Fig. 1). In The Netherlands, Nevobo organizes its recreational competitions in 4 different geographical regions and recreational teams compete against each other within a geographical region. For practical reasons, the two largest competition regions (geographical regions West and East) will be selected for the study and randomly assigned to an intervention region and a control region. This is done to avoid any contamination and competitive bias within a competition region. The expectation is that coaches might be more inclined to participate if the group allocation and thus the volleyball conditions (training and match) do not differ between teams within a competition region. The need for ethical approval was waived by the Medical Ethics Review Committee of the Academic Medical Center because the Medical Research Involving Human Subjects Act (WMO) does not apply to our study protocol (W17_048#17.065; Amsterdam, The Netherlands). The study protocol is registered in the Dutch Trial Registry (ID: NTR6202).

**Fig 1 Fig1:**
[figure not shown]
Anticipated flowchart of participants in the randomized prospective controlled trial

### Participants and recruitment

The participants will be healthy recreational adult volleyball players. Inclusion criteria are: (i) 18 years of age or older; (ii) playing in a volleyball team competing recreationally in a competition region involved in the study; (iii) practicing volleyball (training and/or match) at least twice a week; (iv) speaking and reading Dutch fluently; (v) owning an email address.

Between March and May 2017, coaches of eligible teams will be contacted by the Nevobo and will receive detailed information about the study (purpose and procedures). Subsequently (August 2017), coaches potentially interested in the study will be informed face to face during explanatory group meetings about the purpose of the study, the procedures of the study and their study group allocation. At these explanatory meetings, coaches receive invitation letters about the purpose and procedures of the study for their players. Coaches and players willing to be enrolled in the study will give their informed consent prior the start of the 2017–2018 season, agreeing then to participate voluntarily in the study. The flow of the participants is presented in Fig. 1.

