### Intervention

The intervention ‘VolleyVeilig’ (in Dutch) is made available exclusively to the participants within the intervention group, aiming to prevent or reduce the occurrence of finger/wrist, shoulder, knee and ankle injuries among adult recreational volleyball players. The intervention consists of a warm-up program including more than 50 distinct exercises (with different variations and levels) that should be conducted at least twice a week prior to any volleyball activity (training or match) [10]. The intervention is divided into 6 phases, each lasting 5 to 6 weeks (accordingly to a typical volleyball season), providing volleyball coaches every week with a new warm-up program that shows progressive increments in terms of intensity, frequency, duration and/or complexity. Each warm-up program lasts 15 min and is divided into a preparatory cardiovascular warm-up (2 to 3 min), core stability exercises (2 to 3 min; for instance straight plank), exercises principally directed towards the prevention of knee injuries (4 to 5 min; for instance squat), and exercises principally directed towards the prevention of shoulder injuries (4 to 5 min; for instance external rotation strength with resistance elastic). The exercises directed towards the prevention of ankles injuries (for instance one legged stance) are embedded within each warm-up program. All warm-up programs of the intervention are overseen by the coaches, being available through a website and an application for smartphone/tablet (automatic synchronisation) that are accessible with a username and password. Information and instructions about the exercises are available as texts and video’s (including voice-over). Illustrations of the website and application for smartphone/tablet as well as examples of exercises within the intervention are presented in Fig. 2.

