Players will be asked every two weeks during the 2017–2018 season to complete the translated and modified Dutch version of the Oslo Sports Trauma Research Centre questionnaire (OSTRC) [11, 12]. The OSTRC questionnaire has been proposed and validated to register and monitor sports-related health problems over time, including acute and overuse injuries [13]. The internal consistency (Cronbach’s a) of the OSTRC questionnaire is estimated at 0.96 and 0.91 for overall problems (including illnesses) and overuse injuries, respectively [11, 13]. With this questionnaire, both acute and overuse injuries are registered through four key questions related to: (i) difficulties to participate normally in volleyball activity, (ii) reduced training volume due to injury or complaint, (iii) influence of injury or complaint on performances, and (iv) experienced complaint i.e. symptoms during volleyball during the previous 2 weeks. If no problems are reported on these four key questions, the questionnaire is finished. If an injury or complaint is reported, subsequent questions are asked about location, circumstances, recurrence and return to play. In the present study, acute injury is defined as a sudden event sustained by a player during a volleyball activity (training or match) that results in the player to stop his or her volleyball activity [14, 15]. Overuse injury is defined as a non-sudden event gradual in onset sustained by a player due to participation in volleyball that results in reduced performance and/or ultimately in the player to decrease or stop his or her volleyball activity (training or match) [14, 15]. For the registration of injury, an online form sent by email will be used (anonymous and coded for privacy reason). A reminder will be sent to players after approximately four days in case of no response. Once completed, the online forms will be saved automatically on an electronic server secured according to good clinical practice with forced strong passwords, SSL security and regular backups.

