### Statistical analysis

Descriptive analyses (mean, standard deviation, frequency, range) will be conducted for the different baseline variables in both study groups. To evaluate the success of the randomization and matching, baseline values will be analysed for differences between the intervention and control group (Chi Square, independent T-tests and/or Mann-Whitney test). Total, training and match incidence of acute injury (and its 95% CI) will be calculated by dividing the number of newly incurred acute injuries (excluding re-injuries) identified during the follow-up by the sum of volleyball exposure (total exposure, training exposure and match exposure) in hours until the first injury [14, 15]. For overuse injuries, prevalence repeatedly measured over time is considered the preferable measure [15]. Therefore, the mean prevalence (expressed as percentage) of overuse injuries repeatedly measured over time will be calculated for each 2-week period by dividing the number of participants reporting an overuse injury during that period by the total number of respondents during the same period. Then, mean prevalence (and its 95% CI) will be calculated by dividing all prevalence rates measured every 2 weeks by the number of 2-week periods. Differences in the incidence of acute injury between the intervention and control groups will be assessed using cox regression analysis (significance level set at *p* < .05; adjusted for age and/or gender). Differences in the prevalence of overuse injury between the intervention and control groups will be assessed by comparing their mean prevalence (independent T-tests and/or Mann-Whitney test). Secondary analyses will be conducted to compare the onset of acute and overuse injury between the intervention and control groups based on three levels of adherence (low, medium, high).

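### The overuse comparison counts problems already present before the season and does not adjust for them, although each arm is a single region

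*Protocol article*

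**What the plan says.** Under Participants and recruitment, the Protocol article states: "The participants will be healthy recreational adult volleyball players". The five inclusion criteria that follow are age, team and region, and then "iii) practicing volleyball (training and/or match) at least twice a week; (iv) speaking and reading Dutch fluently; (v) owning an email address". None refers to current or past injury, and no exclusion criterion is given.

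Under Exposure and injury monitoring, the timing of the injury questionnaire is: "Players will be asked every two weeks during the 2017–2018 season to complete the translated and modified Dutch version". No administration before the season is described. The definition reads: "Overuse injury is defined as a non-sudden event gradual in onset sustained by a player due to participation in volleyball". It sets no date after which onset must fall.

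Under Statistical analysis, overuse prevalence for each two-week period is found by "dividing the number of participants reporting an overuse injury during that period by the total number of respondents during the same period", and the period values are then averaged. The arms are compared on mean prevalence by independent t-test and/or Mann-Whitney test. The same section limits the acute outcome to newly incurred injuries, excludes re-injuries, and adjusts its Cox model for age and/or gender. It also says: "Descriptive analyses (mean, standard deviation, frequency, range) will be conducted for the different baseline variables in both study groups". These variables are tested between groups but not listed.

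Under Study design and allocation, two regions are randomised, one to each arm. Under Sample size, teams are matched on competition level only.

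**The concern.** The programme is described as "aiming to prevent or reduce the occurrence of finger/wrist, shoulder, knee and ankle injuries", and the hypothesis is a 40% reduction attributable to it. A player with a long-standing shoulder or knee complaint who still plays twice a week meets all five criteria. That player counts as an overuse case from the first form onwards, in either arm.

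Two things follow:

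- **Bias.** With one region per arm, randomisation cannot be relied on to balance pre-season overuse. Any difference that persists into the season enters the comparison at face value, because the stated test has no baseline term.
- **Dilution.** Cases carried in add to prevalence in both arms. Unless the programme improves them, they pull the apparent reduction towards zero.

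The acute outcome is not affected in this way, because it counts new injuries only.

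**Working it through.** **1. The article's own figure.** Inputs from Sample size: control prevalence 0.25, 40% reduction (so 0.25 × 0.60 = 0.15), 80% power, significance level 0.05, 15% loss. The two-sided two-proportion formula gives 250 per arm. With continuity correction, 250/4 × [1 + √(1 + 4/(250 × 0.10))]² = 62.5 × 2.077² ≈ 270. Then 270/0.85 ≈ 318 per arm, or 636 in total, against the stated 640. The figure reproduces, so this point does not rest on an arithmetic error. The planned difference is 0.25 − 0.15 = 10 percentage points. It serves below only as a yardstick, because 0.25 is a general injury prevalence and not a two-weekly overuse prevalence.

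**2. The two outcomes side by side.**

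| | Acute | Overuse |
|---|---|---|
| Cases counted | newly incurred, re-injuries excluded | every respondent reporting one in the period |
| Stated adjustment | age and/or gender | none |

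The article separates new from existing problems for one outcome and not for the other.

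**3. Bias, under assumed values.** Shift in the difference between arms = regional difference before the season × share persisting through follow-up. The article gives neither input.

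- No regional difference: shift 0.
- 5 points × 0.30 = 1.5 points.
- 5 points × 0.70 = 3.5 points.
- 5 points × 1.00 = 5 points, half of the 10-point yardstick.

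The direction may be either way. Take an assumed new-onset prevalence of 0.175 in the control arm, a true 40% reduction in it (0.105), and full persistence of carried-in cases that the programme leaves unchanged:

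- Carried-in 0.075 in both arms: control 0.250, intervention 0.180; apparent reduction 28%.
- Carried-in 0.10 intervention, 0.05 control: control 0.225, intervention 0.205; apparent reduction 1 − 0.205/0.225 ≈ 9%.
- Carried-in 0.05 intervention, 0.10 control: control 0.275, intervention 0.155; apparent reduction 1 − 0.155/0.275 ≈ 44%.

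**4. Dilution, under assumed values.** Let c be the carried-in share of control prevalence and r the relative reduction that the programme achieves in those cases. Apparent reduction = 0.40 × (1 − c) + r × c.

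- c = 0: 40%, whatever r is.
- c = 0.20, r = 0: 32%.
- c = 0.30, r = 0: 28%.
- r = 0.40: 40% at any c, that is, no dilution.

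Dilution therefore depends wholly on c and r, and the article reports neither.

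**The case against.** Four objections have force.

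- **Baseline data.** A reader might infer that current injury is never recorded before the season. The article does not support that. It mentions baseline variables without listing them, and a condensed article may leave the list to the full protocol. It can only be said that no such measure is stated. What stands regardless is that the stated overuse test would not use one.
- **Prevalence is deliberate.** The article gives its reason for choosing repeated prevalence for overuse injury, and counting existing cases is inherent in that measure. This is accepted. The point is not to abandon prevalence but to account for its level at the start.
- **The programme may help existing problems.** It might shorten complaints or prevent recurrence, and prevalence would capture that. Dilution is therefore conditional, as step 4 shows.
- **Region is confounded with treatment anyway.** One covariate does not cure a design with one region per arm. This is correct. Adjustment removes only the part carried by recorded baseline overuse.

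A reader might also want to turn the dilution into a loss of power. The documents do not support such a figure: 0.25 is not a two-weekly overuse prevalence, and the planned overuse test does not compare two simple proportions.

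The recurrence question asked after a reported problem does not answer the concern, since no use of it is stated for the overuse outcome.

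**Conclusion.** The point holds as a cheap improvement. As written, the overuse comparison includes problems present before the season and takes no account of how the two regions start. A pre-season regional difference would therefore be read as an intervention effect. Its size cannot be derived from the documents. The 1.5 to 5 point shift rests on an assumed 5-point regional difference with 30% to 100% persistence, and the shift is zero if the regions start level. Dilution occurs only to the extent that the programme does not improve existing problems. The word 'healthy' is given no content by the stated criteria. The conclusion concerns the overuse outcome only, and it does not claim that baseline injury goes unrecorded.

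**What to change.** - Administer the existing online injury questionnaire once before the first programme session. If baseline injury status is already collected, say so and use that.
- Replace the unadjusted t-test or Mann-Whitney test with a player-level model of repeated two-weekly overuse status, with baseline overuse injury as a covariate.
- Add a sensitivity analysis in players free of overuse injury at baseline.
- Make 'healthy' agree with the criteria, either by stating what it requires or by removing the word.
- Do not use the first in-season form as a baseline covariate. It is measured after the programme has begun, so adjusting for it may remove part of the effect.

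The cost is one extra online form per player and a regression model in place of a simple test. Coaches learn their allocation at the explanatory meetings, before players consent, so the baseline form may be completed with allocation known. The adjustment reduces the confounding of region with treatment but does not remove it, and the report should say so.

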## Discussion

This article describes the design of a study evaluating the effectiveness of an intervention on the occurrence of finger/wrist, ankle, shoulder and knee injuries among adult recreational volleyball players. This study will be one of the first randomized prospective controlled trials in recreational volleyball that looks at the occurrence of both acute and overuse injuries.

The two major challenges of this study are related to the recruitment of a large number participants and the monitoring of both exposure and injuries. A total of 456 volleyball players across 46 teams (10 players per team on average) and two competition regions are enrolled in the study. The selection of the two largest competition regions in The Netherlands was based on practical reasons. In these two regions, a total of 2797 adult teams across 507 clubs are available, which should be sufficient to reach and enroll 456 participants. Also, holding explanatory group meetings for coaches about the purpose and procedures of the study remains more efficient when those meetings are geographically located nearby the enrolled clubs. For the monitoring of volleyball exposure and injuries, coaches and players are asked to complete an electronic questionnaire every two weeks during the whole 2017–2018 season. Even if not time consuming for most participants (likely to remain uninjured), completing a questionnaire every two weeks remains a substantial task for all participants that might play a role in the recruitment and follow-up of participants as well. However, completing such an electronic questionnaire every two weeks is needed to monitor accurately the occurrence of especially overuse injuries. In sports injury epidemiology, recording overuse injuries has always been a problem as athletes are often likely to continue their sport participation despite their complaints. In our study, the use of the reliable and valid OSTRC questionnaire will allow us to record over time both acute and overuse injuries, adding an unequivocal and unique value to the existing sports injury epidemiological evidence.

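### Coaches learn their arm before they consent and before their players are invited, so the people who enrol can differ by arm and can bias the comparison

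*Protocol article*

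**What the plan says.** Study design and allocation takes two competition regions, which are "randomly assigned to an intervention region and a control region". Participants and recruitment then sets out the following order.

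1. Between March and May 2017 the federation contacts coaches of eligible teams with information on purpose and procedures. Allocation is not mentioned at this step.
2. In August 2017, "coaches potentially interested in the study will be informed face to face during explanatory group meetings". The topics include "the procedures of the study and their study group allocation".
3. "At these explanatory meetings, coaches receive invitation letters about the purpose and procedures of the study for their players".
4. "Coaches and players willing to be enrolled in the study will give their informed consent prior the start of the 2017–2018 season".

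The article describes no consent before disclosure and no recruitment by someone unaware of the arm. Three safeguards bear on comparability: matching of teams on competition level (Sample size), and baseline tests between groups and adjustment for age and/or gender (both in Statistical analysis). The adjustment is stated only for the Cox model for acute injury. The overuse comparison is a t-test or Mann-Whitney test.

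**The concern.** When people decide whether to join after learning their arm, random allocation no longer protects the comparison of those who join. This is the familiar recruitment bias of cluster-allocated trials that enrol after disclosure.

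The arms ask different things of a coach. Intervention coaches receive a programme that controls cannot access, but must run it and report adherence. Controls carry on as usual. Coaches and players in both arms complete forms every two weeks, which the Discussion concedes may affect recruitment and follow-up. Different kinds of teams could plausibly come forward in each region.

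The article itself links allocation to willingness. One of its reasons for allocating whole regions reads: "coaches might be more inclined to participate if the group allocation and thus the volleyball conditions (training and match) do not differ between teams". The teams meant are those of one region. That supports giving all teams in a region the same condition. It does not require naming the condition before consent.

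There is also ample room for self-selection, since the Discussion says that "a total of 2797 adult teams across 507 clubs are available" in the two regions and only a small share is taken.

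**Working it through.** **Inputs from the article.** Control proportion 0.25, 40% reduction (so 0.15), 80% power, significance level 0.05, 15% loss, equal arms and 640 players in 64 teams (Sample size). 456 players in 46 teams and 2797 teams available (Discussion). Sidedness is not stated; two-sided is assumed.

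**The plan's own figure.** With mean proportion 0.20 and difference 0.10, n per arm = [1.96·√(2·0.20·0.80) + 0.842·√(0.25·0.75 + 0.15·0.85)]² / 0.10² = 250, or 270 with continuity correction. Then 270/0.85 = 318 per arm, 636 in total, which rounds up to 64 teams of 10, or 640. The figure reproduces, and this point does not dispute it.

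**Share of teams taken.** 64/2797 = 2.3% as planned; 46/2797 = 1.6% as given in the Discussion.

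**Players per arm after 15% loss.** 640/2 × 0.85 = 272; 456/2 × 0.85 = 194.

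**Illustration A: no true effect.** Control risk is 0.25. Intervention enrolees have an assumed underlying risk p. The chance of a significant result favouring the intervention is Φ[(d − 1.96·SE₀)/SE₁], where d = 0.25 − p, SE₀ = √(2·m·(1−m)/n) with m the mean of the two risks, and SE₁ = √([0.25·0.75 + p(1−p)]/n).

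Example with p = 0.20 and n = 272: m = 0.225, SE₀ = 0.0358, SE₁ = 0.0357. Then (0.05 − 0.0702)/0.0357 = −0.56, and Φ = 0.286.

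| Assumed risk p | Apparent risk ratio | 194 per arm | 272 per arm |
|---|---|---|---|
| 0.25 (no shift) | 1.00 | 2.5% | 2.5% |
| 0.225 | 0.90 | 8% | 10% |
| 0.20 | 0.80 | 22% | 29% |
| 0.175 | 0.70 | 44% | 57% |

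**Illustration B: a true 40% relative reduction, 272 per arm.** The observed intervention risk is 0.6 × p, compared with 0.25 in controls.

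| Assumed risk p | Observed risk | Apparent difference | Apparent risk ratio | Power |
|---|---|---|---|---|
| 0.20 | 0.120 | 13.0 points | 0.48 | 98% |
| 0.225 | 0.135 | 11.5 points | 0.54 | 93% |
| 0.25 | 0.150 | 10.0 points | 0.60 | 83% |
| 0.275 | 0.165 | 8.5 points | 0.66 | 69% |
| 0.30 | 0.180 | 7.0 points | 0.72 | 51% |

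The shifts are assumptions with no source in the article. Clustering is ignored. The calculation uses the season-proportion framing of the sample size section, not the planned Cox model or the mean two-weekly prevalence, so it shows the order of magnitude only.

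**The case against.** The sequence itself is hard to contest. The case on the other side concerns what follows from it, and much of that stands.

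- **Bias has not been shown.** A reader might infer that the comparison is biased, or that injury-prone or prevention-minded teams will gather in the programme arm. The article contains no data on either. The opportunity is built into the design; its occurrence and direction are unknown.
- **Only coaches are said to be told.** The players' letters are described as covering purpose and procedures. Players may hear the arm from their coach, but that is inference. What the text supports is that they are invited through coaches who know it.
- **The first contact is not described as arm-aware.** The spring approach precedes disclosure, so part of the self-selection may be the same in both regions. The final decision still follows disclosure, so this lessens the concern without removing it.
- **Controls may receive something.** The article says only that they have no access to the intervention. It is silent on incentives or later access, so one cannot conclude that they gain nothing by taking part.
- **The size depends on the assumed shift and scale.** A 2.5-point shift gives 8–10%, far less than a 5-point shift. A reader might also say that a 5-point shift hides half of the planned 10-point difference. That is so if control enrolees are at 0.20 and intervention enrolees at 0.25 × 0.6 = 0.15. With controls at the planned 0.25 and intervention enrolees at 0.30, the difference is 7 points, so three-tenths is hidden.
- **Some remedies may already exist.** Baseline variables are not listed, so previous injury may be collected. The article follows CONSORT and has a flowchart that was not available here, so counts by arm may be planned.
- **Reordering does not solve everything.** Coaches run the programme, so arms become known in any case and differences in reporting or drop-out due to that remain. With one region per arm, region stays confounded with arm.

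None of this justifies disclosing allocation before consent.

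**Conclusion.** The point holds as a risk of recruitment bias of unknown direction. Disclosure to coaches, invitation of players through them and consent follow in that order in the text. Competition level, age and gender do not stand in for injury history or motivation, and baseline tests can flag an imbalance but do not correct it.

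On the assumed shifts, a 2.5- to 7.5-point lower underlying risk among intervention enrolees would raise the chance of a false benefit from 2.5% to between about 8% and 57%, depending on the shift and the number enrolled. A 5-point higher risk with a true 40% reduction would shrink the apparent difference from 10 to 7 points and cut power from 83% to 51% at 272 per arm. These figures show sensitivity; they do not estimate bias in this trial.

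The change is worth making because it is cheap. This is a secondary weakness in a design with one region per arm, and it does not by itself invalidate the trial.

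**What to change.** Hold the same explanatory meetings in both regions without naming the allocation. Obtain coach and player consent and baseline data, including injury in the previous season. Close the team list. Only then disclose the allocation and release the programme logins; access is already controlled by username and password (Intervention). Report the numbers of coaches and players approached and consenting in each arm.

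The Discussion describes 456 players as enrolled. If enrolment is indeed complete, reordering is no longer possible. In that case report the same counts by arm, adjust both the acute and overuse comparisons for previous injury where it was collected, and state the order of disclosure and consent as a limitation.

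The cost is a reordering of existing steps plus one later message to teams. The downside is that some coaches may be less willing to sign up without knowing their arm, or may withdraw once told; such withdrawals should be counted by arm. The change will not remove reporting differences due to lack of blinding, nor separate the effect of region from that of arm.
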